### Objectives and outcome measures

The primary objective of Pearl is to determine the performance characteristics of novel state-of-the-art diagnostic approaches for the early diagnosis of HCC in study participants who are diagnosed with HCC by conventional means. For each novel diagnostic approach (whether as a single test or combination of tests) the outcome measures will be the sensitivity, specificity, and positive and negative predictive values in terms of HCC diagnosis for each test. The diagnostic approaches to be tested are as outlined in the section ‘Sample handling and analysis’. Evaluation of the outcome measures will begin once 50 cases of HCC have accumulated within the Pearl cohort.

The primary objective outlined above will be evaluated in conjunction with data from the DeLIVER sister study SELiNa. The Pearl cohort will be divided and used as part of the SeLiNa discovery cohort (providing non-HCC cirrhosis controls), and as the validation cohort (see figure 3).

**Figure 3 F3:**
[figure not shown]
Schematic outlining how the Pearl cohort will be used in conjunction with the SELiNa cohort. HCC, hepatocellular carcinoma.

A key secondary objective of Pearl is to develop prognostic models for ‘risk-stratifying’ patients with cirrhosis according to their future risk of HCC. This could enable clinicians to personalise HCC surveillance. The models developed will be evaluated primarily in terms of their discriminative ability (ie, ability to differentiate individuals who develop HCC from those who do not), measured via the Concordance Index (C-Index). In this context, the C-index will indicate the degree to which individuals who develop HCC have a higher risk score than those who do not.

An additional secondary objective includes quantifying the cumulative incidence of HCC among people with cirrhosis and determining how this varies by underlying cirrhosis aetiology in a UK setting. The cumulative incidence of HCC (stratified by HCC aetiology) will be measured at 1, 3 and 5 years postbaseline.

A further secondary objective will be using the Pearl cohort to identify patients at high risk of developing HCC using the AMAP clinical risk score, for the development of novel MR imaging as part of the separate AMULET study.^31^

### Statistics and analysis

#### Primary objective (evaluate diagnostic performance of early diagnosis assays)

The investigators will assess the performance of selected detection assays for diagnosis of early HCC. This will be achieved by comparing assay values for early HCC cases with those of non-HCC controls (using the SELiNa cohort data). The performance characteristics of primary interest for each assay will be:

Sensitivity (ie, proportion of HCC cases with a ‘positive’ result).Specificity (ie, proportion of non-HCC cirrhosis cases with a ‘negative’ result).Positive predictive value (ie, probability of having HCC for individuals with a ‘positive’ result).Negative predictive value (ie, probability of not having HCC for individuals with a ‘negative’ result).

The area under the receive operating curve, derived from an assay’s sensitivity and specificity, will also be calculated as a summary measure.

As well as quantifying the performance characteristics of each assay in isolation, we will also assess the degree to which performance characteristics may be augmented by combining information from multiple assays into a single ‘multivariable’ model. Simplest methods will be considered first, considering increasingly complex methods if they provide value, for example, logistic regression, random forests, support vector machines.

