The Pearl study aims to create a large UK cohort of 3000 patients with liver cirrhosis, at risk for HCC that will be followed prospectively for 3 years, from multiple National Health Service (NHS) UK sites. The study cohort will be used to assess technologies to detect liver cancer at the earliest stages when curative therapies may be applied and to develop new models using a combination of clinical, molecular and genetic data to identify those most at risk for developing HCC. We hypothesise that the combination of state-of-the-art molecular diagnostics and clinical data can be used for the early detection and risk prediction of HCC.

The Pearl cohort will be part of a broader research programme ‘The early Detection of hepatocellular LIVER cancer (DeLIVER)’ which is funded by a 5-year programme grant from CRUK to the University of Oxford. SELiNa (The detection of Small Early Liver cancer with Natural history follow up study) is a sister study to Pearl within the DeLIVER programme, aiming to recruit 250 patients with small HCC. SELiNa is closely linked to Pearl and the data from both cohorts will be used to help evaluate the state-of-the-art assays being tested (see the ‘Objectives and outcome measures’ section).

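### PPV and NPV are attached to a comparison of separately recruited HCC cases and cirrhosis controls, with no prevalence named; read directly from it, PPV would be too high and NPV too low

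*Protocol article*

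**What the plan says.** Under Objectives and outcome measures, the protocol article states that for each diagnostic approach "the outcome measures will be the sensitivity, specificity, and positive and negative predictive values in terms of HCC diagnosis for each test". Predictive values are therefore two of the four primary outcome measures.

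Under Statistics and analysis, Primary objective, assay performance is to be assessed by "comparing assay values for early HCC cases with those of non-HCC controls (using the SELiNa cohort data". The list that follows includes "Positive predictive value (ie, probability of having HCC for individuals with a ‘positive’ result" and "Negative predictive value (ie, probability of not having HCC for individuals with a ‘negative’ result". No prevalence or incidence is named for either.

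The Introduction describes SELiNa as a sister study "aiming to recruit 250 patients with small HCC". Objectives and outcome measures then gives Pearl two roles: "The Pearl cohort will be divided and used as part of the SeLiNa discovery cohort (providing non-HCC cirrhosis controls), and as the validation cohort". The size of the split is not given in the text, and the figure that illustrates it is not available here.

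**The concern.** PPV and NPV depend on how common HCC is among the people tested. In the comparison described, cases come from a study that enrols people with HCC, and controls come from a cirrhosis cohort that supplies people without it. The ratio of the two is a product of recruitment. Sensitivity, specificity and AUC do not change with that ratio; PPV and NPV do.

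The validation part of Pearl is better placed but not free of the problem. If non-HCC participants are taken out to serve as discovery controls, the case fraction among those who remain rises, by an amount that depends on the undisclosed split.

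Predictive values tell a clinician what a positive or negative result means for a patient with cirrhosis. A PPV that reflects a recruitment ratio would make a surveillance assay look more useful than it is.

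**Working it through.** **Inputs from the protocol article.** SELiNa cases: 250 (Introduction). Pearl: 3000 recruited, about 10% drop-out, 2700 retained (Sample size). About 75 HCC cases expected in 3 years (Abstract) and about 90–180 in 5 years (Sample size). All-cause mortality 5% per year (Figure 4 legend). Standard screening interval 6 months (Introduction).

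**Assumptions.** Sensitivity (Se) 70% and specificity (Sp) 90%, since the article gives neither. The case:control ratios are also assumed, as is an HCC incidence of 1% per year.

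**The plan's own figure first.** With N = 2700, HCC rate r = 0.01, mortality m = 0.05 and t = 3 years, expected cases = N × r/(r+m) × (1 − exp(−(r+m)t)) = 2700 × (0.01/0.06) × (1 − exp(−0.18)) = 450 × 0.1647 = 74.1. This agrees with about 75. The 3-year case fraction is 75/2700 = 2.8%.

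**Formulas.** With case fraction p:

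PPV = Se·p / (Se·p + (1−Sp)(1−p))

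NPV = Sp(1−p) / (Sp(1−p) + (1−Se)p)

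**Results at Se 70%, Sp 90%.**

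| Setting | p | PPV | NPV |
|---|---|---|---|
| 250 cases : 250 controls | 50% | 175/(175+25) = 87.5% | 225/(225+75) = 75.0% |
| 250 : 1000 | 20% | 175/(175+100) = 63.6% | 900/(900+75) = 92.3% |
| 250 : 2700 | 8.5% | 175/(175+270) = 39.3% | 2430/(2430+75) = 97.0% |
| Pearl, 3 years, 75/2700 | 2.8% | 52.5/(52.5+262.5) = 16.7% | 2362.5/(2362.5+22.5) = 99.1% |
| One 6-month round at 1% per year | 0.5% | 0.0035/(0.0035+0.0995) = 3.4% | 0.8955/(0.8955+0.0015) = 99.8% |

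The 250:2700 row is an upper bound on controls. It uses the whole retained cohort, including the 75 future cases, and leaves nobody for validation.

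**Size against Pearl's 3-year fraction.** PPV: 87.5/16.7 = 5.2-fold at 250:250, and 39.3/16.7 = 2.4-fold at 250:2700. NPV is too low by 99.1 − 75.0 = 24 percentage points and 99.1 − 97.0 = 2 points respectively.

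**Sensitivity to the assumed accuracy.** Over Se 60–90% and Sp 80–99%, the smallest PPV ratio is at 90%/99% with 250:2700. There, (225/252 = 89.3%)/(67.5/93.75 = 72.0%) = 1.2. The largest is at 60%/80% with 250:250. There, (150/200 = 75.0%)/(45/570 = 7.9%) = 9.5.

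**Validation part of Pearl.** Suppose only non-cases leave, so that 75 cases and 2625 non-cases are reduced to 75 cases and 2625 − k non-cases.
- k = 250: 75/2450 = 3.1%; PPV = 52.5/(52.5+237.5) = 18.1%.
- k = 1000: 75/1700 = 4.4%; PPV = 52.5/(52.5+162.5) = 24.4%.

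The undivided value is 16.7%. The inflation is slight for a small split and larger for a big one.

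**Why a time window must be stated.** Protocol procedures adds a sample close to HCC diagnosis, while other participants are sampled at baseline and about every 18 months. If cases accumulated over time are set against one pool of controls, crude PPV rises with follow-up even though the assay is unchanged. At the 50-case trigger it is 35/(35+265) = 11.7%. At 75 cases it is 16.7%. At 180 of 2700 it is 126/(126+252) = 33.3%.

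**The case against.** The strongest reply is that Pearl is a prospective cohort and is named as the validation cohort. The primary objective concerns Pearl participants who are diagnosed with HCC, and evaluation begins only after 50 HCC cases have arisen in Pearl. Predictive values could be estimated there. The article also defines PPV and NPV correctly as probabilities and never says that they will be raw sample proportions. Conversion by Bayes' rule is compatible with the text, and the incidence it needs is already a secondary outcome. An estimator is often left to a fuller document.

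Much of this stands. It shows that a valid route exists within the study. It does not show that the article takes that route: the analysis text ties all four measures to the SELiNa comparison, and nothing elsewhere redirects PPV and NPV. The mismatch is between a stated measure and a stated comparison, so it is not merely detail left out.

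Three stronger readings are tempting and are not supported.
- A reader might infer that the cohorts are pooled at a fixed ratio, so that the predictive values are bound to be wrong. The article states neither pooling nor a ratio.
- A reader might infer an order-of-magnitude error. At the assumed 70%/90%, a tenfold PPV error appears only against the assumed 0.5% risk per 6-month round (87.5/3.4 = 26-fold; 39.3/3.4 = 12-fold). It does not appear against Pearl's own 2.8%.
- A reader might infer that both predictive values are flattered. NPV moves the other way, and by much less in relative terms (99.1/75.0 = 1.3-fold at most here).

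**Conclusion.** The point holds as a defect in what the article ties together. PPV and NPV are primary measures attached to a comparison that cannot yield them without an outside risk, and no such risk is named. If they were computed as that section reads, PPV would be overstated about 2.4- to 5-fold against Pearl's expected 3-year case fraction. NPV would be understated by about 2 to 24 percentage points. These sizes rest on an assumed sensitivity of 70%, specificity of 90% and control numbers between 250 and 2700; over the wider accuracy range above, the PPV factor runs from 1.2 to 9.5. The case fraction of 2.8% rests on the article's own forecast.

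The extra inflation in the validation part of Pearl is real in direction if only non-cases are moved out. Its size cannot be fixed without the split. The documents do not establish that the sponsor will calculate predictive values in the wrong data set, only that the text points there and does not point elsewhere.

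**What to change.** State that the comparison of SELiNa cases with Pearl controls yields sensitivity, specificity and AUC only. For PPV and NPV, name one of two sources:

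1. Bayes' rule, applied to the estimated sensitivity and specificity at the HCC risk observed in the whole, undivided Pearl cohort over a stated time window.
2. Direct estimation in the Pearl validation cohort, over a stated time window, with weights that restore any non-HCC participants moved to discovery.

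In either case, report intervals that carry the uncertainty in sensitivity, specificity and incidence.

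The cost is a few sentences in the plan and a little more analysis, with no change to recruitment, visits or samples. The reported PPV will be less favourable.

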Curative HCC therapies (eg, ablation/resection/transplantation) are only offered to patients with early disease (Barcelona Clinic Liver Cancer (BCLC) stages 0 and A). Beyond BCLC-A, the prognosis with all treatment options is poor; chemoembolisation is used for BCLC-B in patients with CP-A, with a mean survival of 2.5 years. Patients with CP-A cirrhosis and unresectable advanced HCC can be offered selective internal radiation therapy with an aim to down-stage the tumours or to bridge systemic medical therapies.^26^ Approved systemic therapies (sorafenib/lenvatinib) improve survival by only 2.3–2.8 months^27 28^ and are used in patients with BCLC-C disease with CP-A. Immune checkpoint inhibitors show antitumour effects in only 15%–20% of patients with HCC.^29^ Therefore, there is an urgent need to develop new strategies to detect HCC at the earliest possible time points when curative strategies may be offered to patients.

Although liver cirrhosis is the major risk factor for HCC, it is unclear why some people with cirrhosis develop HCC, while others do not. HCC is associated with a ‘field effect’ in the cirrhotic liver that predisposes to cancer transformation as evidenced by multiple HCC that arise contemporaneously. However, the pathways to malignant transformation remain unclear. Recent data suggest that malignant transformation in HCC is not primarily driven by archetypal cancer driver mutations.^30^ Furthermore, it is not known if there is a common biological pathway to HCC conversion, regardless of underlying disease aetiology.

Current biomarkers and imaging-driven technologies that aim to identify those most at risk for HCC and to detect HCC at the earliest possible time points are insensitive and outdated. They perform poorly for HCC-EDx and effective strategies for HCC-EDx are, therefore, urgently required. An EDx programme that improved risk stratification and HCC-EDx would significantly enhance the effectiveness of current surveillance programmes.

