### Inclusion criteria

Patients of all genders, age >18 years.Participants are willing and able to give informed consent for participation in the study.Evidence of cirrhosis Child-Pugh A or B (see table 1), with an underlying aetiology of at least one of the following:Chronic HBV infection.Chronic HCV infection.Alcoholic liver disease.MASLD.Haemochromatosis.

**Table 1 T1:** Cirrhosis diagnosis definition

Criteria A or one of criteria B		
Criteria A	Criteria B	
Histological Assessment(Ishak stage 5 or 6)	Validated non-invasive markers of fibrosis including FibroScan, APRI score >2 or ELF score >10.48 or Fibrotest score >0.73.	FibroScan readings should be assessed by aetiology: HBV: ≥10 kPa HCV: ≥14.5 kPa ALD: ≥19.5 kPa MASLD (NAFLD): ≥15 kPa Haemochromatosis: ≥12 kPa
	Evidence of varices at endoscopy or imaging in the context of a patent portal vein	
	Definitive radiological evidence of cirrhosis (ie, nodularity of liver and splenomegaly on ultrasound/CT)	

APRI score: AST to Platelet Ratio Index score

ELF score: Enhanced Liver Fibrosis score

ALDalcoholic liver diseaseHBVhepatitis B virusHCVhepatitis C virusMASLDmetabolic dysfunction-associated steatotic liver diseaseNAFLDnon-alcoholic fatty liver disease

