### Sample handling and analysis

Participants will have blood and urine samples taken on each study visit (both scheduled and unscheduled). The research samples will be collected, have initial processing in the local laboratory and stored (as per sample collection protocol) prior to transfer to Oxford University labs.

Samples are handled and stored as per Human Tissue Act requirements; all samples are labelled with a unique visit ID and will not contain any personally identifiable information. All future subdivisions of the sample will be allocated a new unique barcode. Linking of clinical data to the samples will be possible using unique participant study numbers and visit ID numbers.

The blood samples will be tested for state-of-the-art biomarkers including (but not limited to):

Detection of epigenetic and genetic mutations and copy number variations in circulating tumour DNA.Polygenic risk scores derived from germline genetic sequencing.Detection of autoantibodies to tumour-associated antigens.Protein biomarkers include the L3 isoform of AFP and des-gamma-carboxyprothrombin.Viral sequencing (HBV and HCV).Proteomics and metabolomics.

The urine samples will be analysed for:

Proteomic and metabolomic profiling including steroid metabolic signatures in urine.

Analyses will be carried out in laboratories within the University of Oxford or with collaborators at other academic institutions. Participant consent for these analyses and storage and future use of remaining blood and urine samples for yet unspecified ethically approved research purposes will be sought. Samples will be retained indefinitely.

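### The primary case–control comparison does not condition on cirrhosis aetiology, so a difference in aetiology mix between cases and controls can pass for diagnostic performance

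*Protocol article*

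**What the plan says.** All references are to the Protocol article.

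- **Statistics and analysis, Primary objective.** Performance is assessed by "comparing assay values for early HCC cases with those of non-HCC controls", and the sentence goes on to name the SELiNa data as the source. Sensitivity is the "proportion of HCC cases with a ‘positive’ result" and specificity the "proportion of non-HCC cirrhosis cases with a ‘negative’ result". The AUC is a summary measure. Assays may be combined in models from logistic regression up to random forests and support vector machines. Aetiology is not mentioned.
- **Inclusion criteria.** Patients enter "with an underlying aetiology of at least one of the following": HBV, HCV, alcohol, MASLD or haemochromatosis.
- **Introduction; Objectives and outcome measures.** SELiNa is a sister study of 250 patients with small HCC. Pearl is divided: it supplies non-HCC controls for discovery and also serves as the validation cohort. The approaches to be tested are those listed under Sample handling and analysis, which include viral sequencing for HBV and HCV, proteomics and metabolomics.
- **Where aetiology does appear.** A secondary objective covers the cumulative incidence of HCC and "determining how this varies by underlying cirrhosis aetiology in a UK setting". The Introduction also says that "it is not known if there is a common biological pathway to HCC conversion, regardless of underlying disease aetiology".

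**The concern.** Aetiology can be related both to who is a case and to what an assay reads, by two separate routes.

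1. **Discovery.** SELiNa cases and Pearl controls are recruited separately, and no matching is stated. Their aetiology mixes may differ for reasons unrelated to cancer. The Recruitment section gives one concrete reason: 22 Pearl sites took part in a study of treated HCV cirrhosis whose surviving participants are expected to be eligible, so Pearl controls could be enriched for treated HCV.
2. **Validation within Pearl.** If HCC rates differ by aetiology, incident cases will have a different mix from the participants who stay free of HCC.

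In either case part of the measured separation may come from the underlying liver disease. A flexible multi-assay model can use such a difference in whichever direction it runs. At stake is the choice of assays to carry forward: in a patient whose aetiology is already known, that part of the signal adds nothing.

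**Working it through.** **The plan's own figure.** Inputs: 3000 recruited less 10% drop-out gives N = 2700 (Sample size); mortality m = 5% per year (Figure 4 caption). The HCC rate r is not in the visible text. Expected cases by time T are

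N × r × (1 − exp(−(r + m)T)) / (r + m).

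With r = 1.0% and T = 3: 2700 × 0.01 × (1 − exp(−0.18)) / 0.06 = 74.1, against the stated figure of about 75. The stated 90 to 180 cases at 5 years correspond to r of about 0.77% to 1.56%. No stated figure is wrong, and the same risk formula is used below.

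**Route 1: SELiNa cases against Pearl controls.** Take a binary marker of viral disease with no tumour signal:

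AUC = 0.5 + (viral share in cases − viral share in controls) / 2.

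The shares are assumptions; the article gives none.

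| Viral in cases | Viral in controls | Sensitivity | Specificity | AUC |
|---|---|---|---|---|
| 40% | 40% | 40% | 60% | 0.50 |
| 60% | 40% | 60% | 60% | 0.60 |
| 75% | 40% | 75% | 60% | 0.675 |
| 30% | 50% | 30% | 50% | 0.40 |

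In the last row the controls are the more viral group. A model free to reverse the sign would read 0.40 as 0.60. This route does not need HCC rates to differ by aetiology.

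**Route 2: Pearl cases against Pearl controls at 3 years.** The Introduction gives annual rates for two aetiologies: 1% to 1.8% for cured HCV and 0.25% to 7.6% for MASLD. Rates for the other three and all mixes are assumed. The marker is taken to identify aetiology perfectly. Groups are ranked by case share over control share, and

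AUC = sum over groups of case share × (control share in lower-ranked groups + half the control share in groups tied with it, itself included).

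Example, HCV at 1.8% and MASLD at 0.25% in equal numbers: the 3-year risks are 0.018 × (1 − exp(−0.204)) / 0.068 = 0.0489 and 0.0025 × (1 − exp(−0.1575)) / 0.0525 = 0.0069. HCV is then 87.6% of cases and 48.9% of controls, so AUC = 0.5 + (0.876 − 0.489) / 2 = 0.69.

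| Mix | Annual rates | AUC |
|---|---|---|
| HCV/MASLD 50/50 | both 1.4% | 0.50 |
| HCV/MASLD 50/50 | 1.0% / 0.25% | 0.65 |
| HCV/MASLD 50/50 | 1.8% / 0.25% | 0.69 |
| HCV/MASLD 50/50 | 1.0% / 7.6% | 0.71 |
| Five equal groups | HCV 1.8%, others 1.0% | 0.56 |
| HBV/HCV/alcohol/MASLD/haemochromatosis 10/30/30/25/5% | 1.0/1.4/0.8/1.0/1.0% | 0.56 |
| Same mix | 1.0/1.8/1.0/0.25/1.0% | 0.65 |
| Same mix | 1.0/1.8/0.5/0.25/1.0% | 0.69 |

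**Against sampling error.** Evaluation starts at 50 Pearl cases. With 50 cases and 2650 controls the Hanley–McNeil standard error is about 0.04. An AUC of 0.56 is about 1.4 standard errors from chance (0.06 / 0.042); 0.65 is about 3.5 (0.15 / 0.043).

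**After conditioning.** Take the 60%/40% row and weight viral controls by 0.60/0.40 = 1.5 and non-viral controls by 0.40/0.60 = 0.667. The weighted viral share in controls is 0.40 × 1.5 = 60%, specificity becomes 40%, and AUC = 0.5 + (0.60 − 0.60) / 2 = 0.50. The effective number of controls falls to 1 / (0.4 × 1.5² + 0.6 × 0.667²) = 1 / 1.167 = 86% of those assayed.

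**The case against.** - **The article does not say the results will be pooled only.** A reader might infer a fixed pooled-only analysis, but that would come from silence. Adjustment may be in the SAP or the full protocol, and Figure 3, which shows how the cohorts are combined, is missing. This stands. What remains is that the comparison and its denominators are stated without conditioning and that discovery cases and controls come from different cohorts.
- **A reader might infer that HCC rates are documented to differ by aetiology.** They are not. Two of five annual rates are given, the MASLD range contains the whole HCV range, the MASLD figure is not tied explicitly to cirrhosis, and the difference is itself a secondary question. Route 2 is therefore conditional. Route 1 is unaffected.
- **A reader might conclude that pooled figures in Pearl are wrong and that 0.50 is the only correct answer.** That goes too far. Validation cases and controls arise in one cohort meant to represent UK cirrhosis, so pooled sensitivity, specificity, PPV and NPV are valid for that surveillance population. The aetiology-adjusted AUC answers a different, also legitimate, question.
- **The marker is a worst case.** A perfect aetiology label with no tumour signal is a bounding device. Where HCV has been cleared, viral sequencing is not such a label. How much aetiology the proteomic and metabolomic assays carry is an assumption. Even at the upper end, an AUC of about 0.7 is a weak test, so this alone would not create a convincing one.
- **Patients may have more than one aetiology,** so matching on aetiology is undefined until a rule is given. This stands, and the fix includes one.

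**Conclusion.** The concern holds as a weakness of the stated comparison, not as an error in any figure. Aetiology can inflate the apparent performance of listed assays, most plainly in discovery, where cases and controls come from separately recruited cohorts. Under the assumed mixes and rates a marker with no tumour signal reaches an AUC of about 0.56 to 0.71. The upper part of that range would look clearly better than chance at 50 cases; 0.56 would not. The effect is zero when the mixes are equal.

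The size rests on assumed aetiology mixes, three assumed incidence rates and a perfect aetiology marker, so it shows what is possible, not what is expected. The documents do not support the stronger claims that a pooled-only analysis is fixed, that rates are known to differ, or that pooled validation results should be demoted.

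**What to change.** 1. **Discovery controls.** Frequency-match the Pearl controls to the SELiNa cases on primary aetiology, or weight them to the case mix. State how primary aetiology is assigned when a patient has more than one. Settle this before the control samples are assayed, because the draw is hard to redo afterwards.
2. **Reporting.** In the primary-objective section, add an aetiology-adjusted AUC, in which each case's value is placed in the distribution of controls with the same primary aetiology and averaged over cases. Add sensitivity and specificity on the same basis, beside the pooled figures.
3. **Validation.** Keep pooled sensitivity, specificity, PPV and NPV in the Pearl validation cohort as estimates for the surveillance population. Matched discovery controls reflect the SELiNa case mix and do not replace them.

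**Cost.** Aetiology is an eligibility criterion and so is established at entry; sample size and visits do not change. Intervals become somewhat wider: in the 60%/40% example weighting leaves 86% of the effective controls. Small groups such as haemochromatosis may need combining.
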